## Abstract

Background: Childhood obesity and mental health problems are major public health concerns worldwide. Early-life exposure to green spaces has been shown to promote physical activity, reduce obesity risk, and improve cognitive and emotional development. Schoolyards offer a unique opportunity to promote health, as children spend a large proportion of their time at school. Methods: This quasi-experimental protocol study investigates the effects of transforming gray schoolyards into biodiverse green spaces on children’s health and well-being. Four primary schools in Limburg (Belgium and The Netherlands) were recruited: two intervention schools and two control schools. Children aged 7–12 years were enrolled, with baseline data collected in November 2021 and follow-up measurements scheduled every six months until November 2023. Outcomes include body mass index (BMI) z-score (primary outcome), waist circumference, diet, cognitive performance, psychological well-being, biodiversity knowledge, and physical activity. Data will be analyzed using linear mixed models, and cost-effectiveness analyses will be performed. Expected Results: Improvements in BMI z-scores, cognitive functioning, dietary behavior, and psychological well-being are expected among children in green schoolyards compared to those in control schools. Increased biodiversity awareness and reduced exposure to black carbon are also anticipated. Conclusions: This study is designed to provide evidence on the health impacts of greener schoolyards and contribute to strategies for promoting child development through environmental interventions.

## 1. Introduction

Childhood obesity has emerged as a critical global public health challenge [1]. The development of overweight and obesity in youth is closely linked to lifestyle behaviors, particularly inadequate physical activity (PA) and unhealthy dietary patterns [2]. Recent estimates from the World Health Organization indicate that in 2022 more than 390 million individuals aged 5–19 years were classified as overweight, including 160 million with obesity. This number reflects a 12% increase in prevalence among children and adolescents since 1990, signaling a rapid upward trend [3]. Such figures are cause for concern, as excess adiposity significantly elevates the risk of cardiometabolic conditions, including cardiovascular disease, type 2 diabetes, and several cancers [2,4]. Beyond physical health, obesity coincides with a broader rise in mental health difficulties among young people worldwide [5], which can adversely affect educational outcomes, overall well-being, and long-term development. According to UNICEF, approximately 86 million adolescents aged 15–19 years and 80 million children aged 10–14 years currently experience mental disorders [6].

Exposure to natural environments during childhood has been associated with multiple dimensions of healthy development. Empirical studies indicate that contact with green space can support emotional well-being, enhance neurocognitive functioning, and foster positive social-behavioral outcomes [7,8,9,10]. In addition, regular interaction with green environments has been linked to favorable physical health indicators, including higher levels of physical activity [8,10,11], improved respiratory function [12], lower body mass index [10,13], and reduced risk of overweight and obesity [8,10,13]. Because lifestyle patterns established early in life often continue into adulthood, interventions that encourage healthy habits during childhood are considered particularly impactful [14]. Promoting such behaviors from a young age has the potential to contribute to both improved health trajectories and academic performance later in life [15]. Given that children spend a substantial portion of their daily lives at school, creating greener schoolyard environments offers a promising strategy to strengthen their engagement with nature and support healthier developmental outcomes. Schools are considered important environments for promoting healthy habits at an early age for several reasons. First, schools can reach all children from diverse backgrounds in a relatively short period. Second, the structured school environment facilitates the implementation of interventions. Moreover, children spend a significant portion of their day here, often with one or two meals. Schools also provide opportunities for PA and health education [16,17]. By constantly exposing children to elements of a healthy lifestyle at school, unhealthy behaviors can be changed [6,17].

The Healthy Primary School of the Future (HPSF) is a Dutch initiative integrating structured physical activity and school-provided healthy meals into the daily routine. Previous evaluations showed favorable effects on children’s lifestyle behaviors and BMI z-scores. More details on the HPSF framework and outcomes have been published elsewhere [15,18].

Building on the foundation of the Healthy Primary School of the Future and existing evidence on the value of natural environments, the Green Healthy Elementary School of the Future initiative was conceived to expand the focus of school health promotion. This program aims to evaluate how transforming conventional playgrounds into biodiverse, nature-rich spaces influences children’s physical and mental health, particularly through opportunities for sensory and exploratory play. The intervention is grounded in the socio-ecological model of school health promotion [19], which emphasizes that behaviors are shaped not only by individual characteristics, but also by broader contextual factors, including social relationships, cultural norms, economic circumstances, and physical environments. According to Bell and Dyment, a green schoolyard is defined as an extracurricular environment where natural elements such as trees, flowers, sand, water, grass, hills, and shrubs are combined to create a more attractive schoolyard and improve the quality of children’s (play) experiences [20].

Several theoretical frameworks help explain why exposure to biodiverse natural environments may benefit children’s health and development. The Attention Restoration Theory (ART) proposes that natural settings support the recovery of directed attention by providing softly fascinating stimuli, which may improve cognitive functioning and learning outcomes [21]. Similarly, the Stress Reduction Theory (SRT) posits that contact with natural environments can evoke psychophysiological stress recovery, thereby enhancing emotional well-being and reducing mental fatigue [22,23]. In addition, the Biodiversity Hypothesis suggests that exposure to diverse natural microbiota may beneficially influence immune function through microbial-mediated training pathways, with potential implications for respiratory health and environmental exposure processing [24,25,26,27,28,29,30,31,32]. These frameworks collectively support the inclusion of outcomes such as cognitive performance, psychological well-being, PA, and biomarkers of environmental exposure, including black carbon in the present study.

Despite the growing evidence for the benefits of green spaces on children’s development, substantial knowledge gaps remain. Most existing studies are cross-sectional or short-term and focus primarily on general neighborhood greenness rather than on biodiverse, intentionally designed school environments [7,8,9,10,11,19,33,34,35,36]. Few studies have simultaneously assessed ecological features, such as quantified biodiversity, together with cognitive outcomes, psychosocial well-being, PA, and environmental exposure biomarkers. Importantly, no previous schoolyard greening protocols have integrated biodiversity assessments with objective measures of black carbon as an internal exposure marker or combined these with detailed cognitive testing in a longitudinal framework. As a result, the mechanisms through which biodiverse schoolyards may influence child health, including potential pathways described in the Attention Restoration Theory, Stress Reduction Theory, and Biodiversity Hypothesis, remain insufficiently understood [19,21,22,23,33,34,35]. The present study addresses this gap by employing a multidisciplinary, longitudinal protocol that captures ecological, behavioral, physiological, and environmental indicators within the same analytical framework.

In the current explorative study, we aim to investigate whether renovating a schoolyard to increase biodiversity has an effect on children’s BMI Z-score, waist circumference, dietary behaviors, health markers, cognitive performance, knowledge and appreciation of biodiversity, and (school) well-being, compared to children in control schools. Additionally, we will compare the effect of a green schoolyard on children’s PA with the partial HPSF.

## 2. Materials and Methods

### 2.1. Study Design and Setting

This study follows a quasi-experimental design involving two intervention schools undergoing schoolyard greening and two comparison schools without environmental changes. All participating schools are primary schools situated in the Province of Limburg of Belgium and The Netherlands (Figure 1). These provinces are characterized by a low SES, compared to the means of the countries [36,37]. ClinicalTrials.gov identifier (NCT number): NCT04898439. Baseline data collection was completed prior to the start of the intervention, with all baseline measurements conducted in November 2021.

School and subject recruitment. Two schools actively participate in the process of greening the schoolyard (one in Belgium and one in The Netherlands). Two other schools in the nearby region are control schools (one in Belgium and one in The Netherlands). Randomization was not possible due to the necessity for complete voluntary cooperation and participation of the intervention schools in greening the schoolyard. Because participation in the greening intervention required voluntary school commitment and alignment with construction timelines, randomization was not feasible. Therefore, potential confounders at both the child and school level will be measured and adjusted for in the linear mixed models. Baseline measurements were completed in November 2021 (T0). Follow-up measurements were planned each half-year for two years until November 2023 (T6: May 2022, T12: November 2022, T18: May 2023, and T24: November 2023). In The Netherlands, not all measurements could be taken due to practical reasons.

Intervention school recruitment. In early 2021, a newspaper call in The Netherlands recruited nine schools from Limburg to green and diversify their schoolyards. These schools were interviewed, and one was selected to participate as an intervention school on the basis of feasibility criteria and the comparability of the schoolyard size and characteristics. Selection of the Belgian intervention and control school was performed by the ‘Provinciaal Natuurcentrum Hasselt’ based on their call to green schoolyards and make schoolyards more biodiverse the comparableness of the schoolyards and number of enrolled students. The recruitment of the intervention schools was completed in September 2021.

Control school recruitment. The schools that voluntarily agreed to participate were selected on the basis of the following inclusion/exclusion criteria: a high pavement-to-greenery ratio and a location in the proximity of the intervention schools with comparable populations and SES backgrounds.

Subject recruitment. Children were recruited for the baseline measurement through informational brochures sent via mail and reminders from the school staff. Furthermore, the research team visited all classrooms to provide information about the study and encourage participation. All children aged 7–12 from both intervention and control schools were eligible for inclusion in this study. Before the baseline examination, written consent from the parents was obtained and children gave their oral permission to participate. The enrollment of children for the initial measurement was concluded in November 2021.

Intervention. Both intervention schools underwent a greening procedure increasing biodiversity, in which they adjusted the gray schoolyard into a green biodiverse schoolyard consisting of (i) the creation of adventurous and diverse play areas, (ii) the establishment of green rest areas, (iii) the planting of flowers, shrubs, hedges and/or trees, and/or (iv) variation in activity zones such as farm animals, pools or vegetable gardens.

Because the greening intervention was implemented by two different schools and included varying components, such as water features, gardens, and diverse vegetation, some heterogeneity in intervention intensity is expected. As each country (Belgium and The Netherlands) includes one intervention and one control school, the correction for country as fixed factor captures unmeasured differences between schoolyards.

### 2.2. Outcome Parameters

Table 1 shows an overview of all outcome measures collected in children and parents/caregivers. The administration of questionnaires that were completed by the children were taken collectively during regular classes. The children independently read and completed the questionnaires. Throughout this process, at least one researcher was present to oversee and address any queries. The anthropometric measurements were taken individually. Tailored questions, accompanied by various graphical illustrations, were utilized in the lunch and general questionnaire. The cognitive performance of children was assessed during regular classes in a separate room. To prevent excessive burden on children and school staff, the majority of child-related measurements were scheduled within a regular school week.

Personal characteristics questionnaire. The parents filled out a questionnaire before the baseline examination to collect information about parental education, parity, ethnicity, parental occupation, income, household smoking behavior, illness, socio-economic demographics, birth date of the child, sex of the child, and the use of medication. Completion of privacy-sensitive questions, such as parental BMI, socio-economic status, and disease status, were optional.

Strengths and Difficulties Questionnaire (SDQ). At each examination, a parent completed the Strengths and Difficulties Questionnaire (SDQ) to assess the child’s emotional and behavioral well-being [38]. The validated SDQ includes five subscales: emotional symptoms, conduct problems, hyperactivity/inattention, peer relationship problems, and prosocial behavior. The first four subscales contribute to a total difficulty score, with lower scores indicating fewer social-emotional difficulties. Responses are scored on a three-point scale (0–2).

(Psycho) social functioning. The self-reported, Dutch-validated KIDSCREEN-52 questionnaire assesses quality of life in children and adolescents across 10 domains, including physical and emotional well-being, self-perception, relationships, school life, autonomy, financial well-being, social support, bullying, and psychological well-being [39,40]. Each of the 52 items is weighted and summed into raw subscale scores, which are then converted into standardized T-scores, with higher scores indicating better quality of life. Additionally, attention bias was assessed using the Tobii po Nano eye tracker (Tobii, Stockholm, Sweden), based on emotion recognition from facial expressions as described by Goeleven et al. [41]. Bias was calculated as the ratio of first fixation duration on ‘happy’ versus ‘anxious’ and ‘sad’ emotional faces.

### 2.3. Food Intake

Food intake is assessed using a combination of a food frequency questionnaire and a dietary recall tool, which are completed by both children and parents. “The food intake questionnaire, tailored specifically for this target group, is based on the Short Dutch Questionnaire to Measure Total and Saturated Fat Intake and the Short Dutch Fruit and Vegetable Intake Questionnaire developed by Van Assema et al. [42,43].” It includes items on fruit and vegetable consumption, soft drinks, sports and energy drinks, and snacks. Dietary recall is employed to evaluate the composition of breakfast and lunch, with questions about lunch intake asked in the classroom immediately after the lunch break. To prevent influencing children’s dietary habits, they are not informed in advance that they will be questioned about their food consumption.

### 2.4. Knowledge and Affinity to Biodiversity

The custom-designed biodiversity questionnaire (Appendix A) generated a score that was used to determine knowledge and affinity for nature and biodiversity. A higher score means a higher affinity for nature.

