## Appendix A. Biodiversity Questionnaire

### Appendix A.1. Perception Section

**Q1a** Do you have pets? (Check the appropriate box)
  Yes = 1
  No = 0
**Q1b** If yes, which animals and how many? (Check the appropriate box and indicate how many)
  Dog = 1
  Cat = 2
  Hamster = 3
  Rabbit = 4
  Fish = 5
  Gerbil = 6
  Reptile = 7
  Bird = 8
  Sheep = 9
  Horse or pony = 10
  Chicken = 11
**Q2** Do you have a garden at home? (Check the appropriate box)
  Yes with grass = 2
  Yes without grass = 1
  No, we don’t have a garden = 0
  (Also analyzed as a two-level factor: yes = 1 no = 2)
**Q3** What do you think about nature? (Check the appropriate box)
  Scoring on a five-point Likert scale: 5 = “I really love nature” 4 = “I just like nature” 3 = “Nature is OK” 2 = “I don’t like nature” 1 = “I hate nature”.
**Q4** Do you think it is important to feel connected to nature?
  Scoring on a five-point Likert scale: 5 = “very important” 4 = “important” 3 = “neutral” 2 = “not important” 1 = “not important at all”
**Q5** Do you think it is important to take care of nature? *
  Scoring on a five-point Likert scale: 5 = “very important” 4 = “important” 3 = “neutral” 2 = “not important” 1 = “not important at all”
**Q6** Do you sometimes see animals in the garden? *
  Scoring on a five-point Likert scale: 5 = “very often” 4 = “often” 3 = “sometimes” 2 = “rarely” 1 = “never”
**Q7** For each of the following questions, indicate yes or no *
  **Question**	**Axis**	**Score If Answered ‘yes’**
  Do you love animals?	Affect	1
  Are you afraid of animals?	Affect	−1
  Can you earn money with animals?	Utility	1
  Are wild animals a nuisance?	Utility	−1
  Would you be sad if animals no longer existed?	Affect	1
  Are animals important to keep nature healthy?	Utility	1
  Do you hate animals?	Affect	−1
  Would people be better off without animals?	Utility	−1
**Q8** What do you think of your playground?
  Scoring on a five-point Likert scale: 5 = “very fun” 4 = “fun” 3 = “average” 2 = “not so fun” 1 = “not fun at all”
**Q9** Where do you prefer to play on the playground? (open answer)
**Q10** Do you think the playground resembles nature with lots of grass, trees, flowers, water, sand, and animals? *
  Scoring on a five-point Likert scale: 5 = “yes, very much” 4 = “yes, a lot” 3 = “average” 2 = “no, a little” 1 = “no, not at all”
**Q11** Do you think more should be done to protect nature, plants, and animals? * Indicate yes or no
  Yes
  No

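### Unless Q8 and Q10 are kept out of the biodiversity score, a rise in greened schools may show only that children noticed the new schoolyard

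*Protocol article*

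**What the plan says.** Section 2.4 describes this outcome in two sentences. The custom questionnaire in Appendix A "generated a score that was used to determine knowledge and affinity for nature and biodiversity", and "A higher score means a higher affinity for nature". It gives no item list, weights or subscores.

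Two items in Appendix A.1 are about the schoolyard:

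- Q10: "Do you think the playground resembles nature with lots of grass, trees, flowers, water, sand, and animals". It is coded 1 to 5, with 5 the most nature-like, and carries an asterisk.
- Q8: "What do you think of your playground". It is coded 1 to 5, with 5 the most fun, and carries no asterisk.

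The asterisk also stands on Q5, Q6, Q7, Q11 and Q12. The text shown does not explain it.

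Section 2.1 says of the intervention schools that "they adjusted the gray schoolyard into a green biodiverse schoolyard". The comparison schools had no environmental change and were chosen for a high share of paving. The Introduction lists knowledge and appreciation of biodiversity among the outcomes to be compared with control schools. Section 2.10 analyses numerical outcomes with the mixed model used for the primary outcome: group, time, group*time and country.

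**The concern.** Q10 is close to a check that the intervention was delivered. Its list of features is grass, trees, flowers, water, sand and animals. The first five appear in the Introduction's definition of a green schoolyard, and farm animals appear among the intervention components in section 2.1. A child who answers Q10 accurately before and after greening will move up the scale, and a child in an unchanged paved yard has no reason to. Q8 rates the same site and may move the same way.

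If these items are part of the score, the group*time term mixes two things: the change made to the yard, and any change in the child's affinity or knowledge. Only the second is the outcome. The Abstract already expects biodiversity awareness to rise, so a difference driven by Q10 would look like confirmation.

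**Working it through.** **1. The plan's own figure.** The article gives no figure for the biodiversity score. Its only power statement (section 2.9) is that effects of 0.52 to 0.63 are detectable with 40 to 60 children per group at 80% power and α 0.05. For a two-sided comparison of two means without clustering, d = (1.960 + 0.842) × √(2/n):

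- n = 40: 2.802 × √(2/40) = 0.626 (0.634 with the t distribution)
- n = 60: 2.802 × √(2/60) = 0.511 (0.516 with the t distribution)

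The stated range reproduces, so it can serve as a yardstick.

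**2. Share of the score range due to Q10.** Range widths, from the printed codes unless marked as assumed:

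- Q3, Q4, Q5, Q6, Q8 and Q10: 4 each (1 to 5)
- Q7: 8 (four statements at +1 and four at −1, so −4 to +4)
- Q1a: 1; Q2: 2
- Q11: 1 (assumed 0/1)
- Q12: 12 (assumed one point for each of 12 pictures)

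| Assumed scoring | Range | Q10 share |
|---|---|---|
| Asterisked items (Q5, Q6, Q7, Q10, Q11, Q12) | 4+4+8+4+1+12 = 33 | 4/33 = 12% |
| Asterisked items without Q12 | 21 | 4/21 = 19% |
| All closed items (adds Q1a, Q2, Q3, Q4, Q8) | 33+1+2+4+4+4 = 48 | 4/48 = 8% |
| All closed items without Q12 | 36 | 4/36 = 11% |

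If Q10 is not scored, its share is 0.

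**3. Spurious effect from Q10 alone.** Suppose Q10 rises by s points in the intervention schools only and every other item is unchanged. The standardized difference is d = s / SD of the score. The SD is not in the article; 3 to 6 is assumed. Each cell gives d, then the probability of declaring an effect with 40 and with 60 children per group (two-sided α 0.05). With no artefact that probability would be 0.05.

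| Rise in Q10 | SD 3 | SD 4 | SD 5 | SD 6 |
|---|---|---|---|---|
| 1 point | 0.33; 0.32, 0.45 | 0.25; 0.20, 0.28 | 0.20; 0.14, 0.19 | 0.17; 0.11, 0.15 |
| 2 points | 0.67; 0.85, 0.95 | 0.50; 0.61, 0.78 | 0.40; 0.43, 0.59 | 0.33; 0.32, 0.45 |
| 3 points | 1.00; 0.99, 1.00 | 0.75; 0.92, 0.98 | 0.60; 0.77, 0.91 | 0.50; 0.61, 0.78 |

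This is a simple two-group comparison of independent children, not the planned mixed model. It shows the order of magnitude only.

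**4. Reading the result.** A 1-point rise stays below the detectable range of 0.52 to 0.63 at every SD tried. A 2-point rise exceeds that range at SD 3 and falls below it at SD 4 to 6. The direction of the bias is clear once Q10 is scored; its size is not.

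**The case against.** The strongest reply is that the article never says which items make up the score, so criticism of any particular sum is criticism of the reader's own rule. Some selection must exist: the pet codes in Q1b are labels and Q9 is open text, and neither can be summed. The appendix separates a perception section from a knowledge section, and Q7 has labelled axes, which hints at subscores. An article may leave detailed scoring to the full protocol.

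Much of this stands, and it rules out several stronger readings that a reader might infer:

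- *That greening necessarily raises the score, or that a significant result is nearly guaranteed.* Inclusion of Q10 is not stated, and the probabilities above run from 0.11 to 1.00 depending on assumptions.
- *That pets and garden contaminate the score.* Nothing says they enter it. Q2 is described as "Also analyzed as a two-level factor: yes = 1 no = 2", which suggests a grouping variable. For a factor the level labels are arbitrary, so the reversed order relative to the three-level code is not an error.
- *That the playground items are about a quarter of the score.* Q8 and Q10 are 8 of 33 points (24%) only for a sum of Q3 to Q8, Q10 and Q11. Adding the 12 points of Q12 gives 8/45 = 18%, and the inclusion of Q8 is itself an assumption.

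What does not fall is the core. The article prints the instrument and states how the resulting score is to be interpreted; the problem lies in that interpretation, not in missing detail. On the plain reading of section 2.4 Q10 counts. If the asterisk marks scored items, Q10 still counts and only Q8 drops out. Removing Q10 needs an exclusion rule that the article does not give.

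**Conclusion.** The point holds conditionally. If Q10 is part of the score, a group*time effect cannot be read as higher affinity or knowledge, because part of it would record that the yard was greened. Q8 adds to this if it is scored too.

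The size is uncertain. Q10 makes up about 8% to 19% of the range under the four scorings tried, and a 2-point rise gives d of about 0.33 to 0.67. These figures rest on an assumed item list, an assumed score SD of 3 to 6 and an assumed rise in Q10, none of which is in the article.

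The consequence is limited to this outcome. The Abstract, section 2.5 and section 2.10 do not name it as primary, and the study is declared exploratory. The BMI z-score analysis is unaffected.

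**What to change.** - Name the items that form each biodiversity score, and say what the asterisk means.
- Keep Q10 and Q8 out of the affinity outcome. Report them separately as perception of the schoolyard, where a rise in intervention schools is a useful check that the greening was noticed.
- Analyse two scores in place of one: affinity from Q3 to Q7 and Q11, and knowledge from Q12 as the number correct. Q6 asks about animals seen in the garden and is less clearly an attitude item, so a check without it would be reasonable.

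The cost is rescoring of data already collected, a slightly shorter scale and one more outcome to report. If Q8 and Q10 are already left out of the score, one sentence in section 2.4 saying so would settle the bias.
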